### Data management, randomization, statistical power, and data analysis

All trial data are gathered through web-based data entry sheets (www.bravo-trial.com) by research nurses/assistants. Data management is the responsibility of the Department of Child Health/Center for Clinical Epidemiology and Evidence-Based Medicine (CEEBM) Faculty of Medicine University of Indonesia/Cipto Mangunkusumo National General Hospital in Jakarta, Indonesia. All investigators who belong to the BRAVO study group have access to the final trial database through the data manager ([name]). Local principal investigators ([name], WI) are also granted direct access to the trial database for monitoring. Public availability of clinical trial data is a pending debate [54] and until decided, any BRAVO data usage is decided by consensus of the BRAVO study steering committee ([name], [name], SS, WI, and [name]). Randomization is centrally performed using computer-based random lists for simple parallel groups. All participating women are given individual study numbers, and their personal information is collected, shared, and maintained in order to protect confidentiality before, during, and after the trial.

BRAVO is restricted to pregnant women who, from their own free will, plan to give breastfeeding for no longer than 2 months, if at all. Forty percent of all pregnant women were estimated to meet that criterion. Thus, for every four eligible women, 10 pregnant women have to be screened, assuming that the number of women lost to exclusion is negligible. The effect of the empowerment program on the increase of exclusive breastfeeding was the first required estimate. From a Southeast Asian trial that used no restrictions on women’s plans to breastfeed for short times, exclusive breastfeeding proportions in the experimental group were expected to be at least 1.5 times higher than in the care-as-usual group. This relative risk was reported throughout the first 6 neonatal months but decreased from 83 % to 53 % at 14 days postpartum and ultimately to 20 % in the experimental group, and to 0 % in the usual-care group at 6 months. In 5-year-old healthy children, breastfeeding versus formula feeding was suggested to have an effect on carotid artery wall intima-media thickness of 20 μm, at an average CIMT of 386 μm (SD 37). Translating to BRAVO, a comparison of 54 women in an exclusive breastfeeding group and 54 women in an exclusive bottle-feeding group would allow detection of a 20-μm group difference in carotid IMT, with 80 % power and alpha = 0.05. Obviously, BRAVO does not yield randomized groups of exclusive breastfeeding and exclusive bottle-feeding groups. Due to contemporary uncertainties about the effects of empowerment on breastfeeding and ultimately on the cardiovascular system, it was assumed that a group that was at least ten times bigger was to be randomized. BRAVO, therefore, aimed to randomize 1000 eligible pregnant women, requiring screening of approximately 2500 pregnant women. A trial of 1000 women can detect small differences in breastfeeding practices between intervention groups. An estimated 500 women randomly allocated to each group would allow for the statistical detection of a nominal difference of almost 10 % in exclusive breastfeeding proportions, with 90 % power and a statistical significance level of 0.05 (PASS 2008). From a public health point of view, a difference of 10 % or higher was considered meaningful.

With respect to data analysis, both descriptive and baseline prognostically important characteristics will be tabulated against intervention strategy. The chance of successful exclusive breastfeeding for 6 months (yes/no) will be compared between the empowerment and care as usual group by calculating the relative risk with 95 % confidence intervals. As an absolute risk estimate to support public health policy making, the number needed to treat (by breastfeeding empowerment) and 95 % confidence intervals will be calculated. The duration of breastfeeding will be studied as a function of the interventions by using linear regression with (transformed) duration as the dependent variable and a group indicator as the independent variable. Should there be post-randomization differences that would hamper proper interpretation, regression modeling will be used to adjust all findings for baseline prognosis (propensity score or inverse probability weighting techniques).

The effects of intervention on cardiovascular measurements will be studied using linear regression techniques with cardiovascular measurements as the dependent variables and a group indicator variable as the independent variable. All regression models will also be used for adjusting for baseline noncomparability when necessary. All analyses will be performed according to the intention-to-treat principle, such that all randomized women will be analyzed by their randomized allocation. Possibly, biased missingness of the 5-year outcome data will be assessed using additional tables of baseline data comparing the available and missing data, and the above-described analytical techniques will be applied for dealing with prognostic group differences [55]. Missing data will be analytically addressed using multiple imputation regression techniques.

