Indonesia is a low-income to middle-income country with a population of 250 million and 4 to 4.5 million births per year. Indonesia lags behind WHO recommendations with only 15 to 40 % exclusively breastfeeding [41–43]. Indonesia is experiencing an epidemiological transition, and it is among the regions identified to face a strong rise in noncommunicable diseases, including atherosclerotic disease and a significant prevalence of chronic obstructive pulmonary disease [44, 45]. Much potential exists for an improvement of breastfeeding practices, as breastfeeding empowerment programs have been shown effective in various Southeast (SE) Asian countries, although not in Indonesia [46–48]. Modifiable predictors of nonexclusive breastfeeding in SE Asian countries have been identified and include the absence of prenatal breastfeeding planning, working by mothers, and the noninvolvement of fathers in the breastfeeding planning [49]. Generally, breastfeeding-promotion programs are probably more successful in achieving exclusive breastfeeding in lower income countries like Indonesia than in economically more affluent societies [50]. Nevertheless, due to the specific local mix of cultures, religions, ethnic backgrounds, and limited resources, the effectiveness of empowerment programs that worked elsewhere, even in SE Asia, cannot be taken for granted in Indonesia.

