### Results of screening, enrollment, and preliminary follow-up

Table 5 shows the characteristics of women who were screened for BRAVO. The ages of the included and excluded women were similar. Included women were more often of low socioeconomic status. Although there was no statistically significant difference in the proportion of working mothers between the excluded and included women, included women more often had blue-collar employment. So far, the 1-year follow-up is 90.1 % complete.

**Table 5 Tab5:** Characteristics of screened women (*n* = 1234)

	Excluded *N* = 707	Included *N* = 527	*P* value
Age	31.3 (5.7)	30.3 (5.9)	0.30^1^
Socioeconomic status			<0.001^2^
Low	78 (12.7)	117 (22.9)	
Middle	432 (70.5)	358 (70.1)	
High	103 (16.8)	36 (7)	
Number of pregnancy			0.70^2^
1	233 (37.8)	212 (41.2)	
2	218 (35.3)	173 (33.7)	
3	112 (18.2)	87 (16.9)	
>3	54 (8.8)	42 (8.2)	
Working mother	213 (34.6)	152 (29.7)	0.08^2^
Blue-collar job	49 (23.9)	55 (37.7)	0.006^2^
Previous breastfeeding	310 (43.8)	248 (47.1)	0.14^2^

Values are means with standard deviations for continuous variables and percentages for frequencies. In case of skewed data (*), the median with the interquartile range was presented

^1^Independent samples *t*-test, ^2^Chi-Square test

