A strong feature of BRAVO is the number of individually randomized pregnant women; to our knowledge, this trial is one of the larger of its kind in a low-resource setting. The principal aim of BRAVO, which is to study the effects of breastfeeding on the early life development of cardiovascular function and structure, sets it apart from other trials that were primarily designed to measure the effects of empowerment on breastfeeding proportions. A major challenge in trials is to achieve accurate and complete follow-up. This is particularly challenging in BRAVO, as it deals with young families in a highly mobile culture. In BRAVO, the follow-up, to be done for the first year of life, is designed to follow regular care (vaccination scheme), is proactive, and includes home visits. So far, follow-up completeness is satisfactory, although the final results will have to be awaited. BRAVO, like all other breastfeeding trials, is pragmatic, so its ultimate success depends on the contrast in breastfeeding between intervention arms that can be achieved. This contrast will still be a function of distributions of breastfeeding duration in both arms and, importantly, on the distributions of bottle and other infant feeding in both arms. Obviously, BRAVO registers breastfeeding duration in both arms as well as the introduction of other feeding habits. The fact that BRAVO, as with other trials, can only study cardiovascular effects as a function of the overall breastfeeding contrast is a limitation that cannot be circumvented by design. On the other hand, the pragmatic character of BRAVO will allow for easier implementation of beneficial results, if found. In principle, a threat to the BRAVO design is that women who are randomly allocated to care as usual will, knowing about the study objectives, change their breastfeeding plans, thus leaving a smaller contrast between the experimental intervention arms. An alternative would have been pre-randomization (first randomize, then obtain informed consent), such as done in Zelen’s design [56]. However, since BRAVO focuses on women who during pregnancy have already planned to provide for a maximum period of 2 months breastfeeding, pre-randomization, with its associated medical ethical implications, was not considered necessary. In BRAVO, individual women are randomized, rather than clusters of women within, for instance, primary care practices. Monitoring of breastfeeding motivation takes place on an individual basis and is performed by the study nurses. The effects of close monitoring are not expected to go easily for all pregnant woman. Although, in principle, a risk of intervention contamination exists, BRAVO uses individual rather than cluster randomization for a couple of reasons. First, the full intervention, both prenatal, perinatal, and postnatal, is well outside the realm of usual care, as it requires high levels of organization (group counseling, home visits). Although cluster randomization was considered, only limited numbers of clusters were feasible in the BRAVO setting, which would have substantially increased the chance of baseline prognostic noncomparability, a much bigger threat to the overall purposes than contamination. A cluster-randomized design would have required larger numbers of pregnant women, in whose offspring highly specialized cardiovascular and respiratory measurements were considered unfeasible. Finally, a cluster-randomized design bears intrinsic prior uncertainties, such as ultimately achieved (differences in) cluster sizes and unknown within-cluster correlations. Although such variation can be dealt with in analysis, the BRAVO design with individual randomization was considered a priori a more robust approach, specifically concerning its overall aim, the study of cardiovascular and cardiometabolic consequences of breastfeeding.

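### The 90 % power statement for exclusive breastfeeding counts every woman allocated and allows for no missing outcomes; at 90 % to 95 % known outcomes, power for the same difference is about 87 % to 88.5 %

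*Protocol article*

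**What the plan says.** All the planning figures are in the protocol article under Data management, randomization, statistical power, and data analysis.

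- The size of 1000 is a multiple of a small carotid comparison (54 versus 54): "it was assumed that a group that was at least ten times bigger was to be randomized".
- The power for the breastfeeding outcome is then given for that size: "An estimated 500 women randomly allocated to each group would allow for the statistical detection of a nominal difference of almost 10" per cent, "with 90 % power and a statistical significance level of 0.05 (PASS 2008").
- The yardstick follows: "a difference of 10 % or higher was considered meaningful".
- No control rate is attached to this calculation. The paragraph cites a Southeast Asian trial in which rates fell "ultimately to 20 % in the experimental group, and to 0 % in the usual-care group at 6 months". The Background gives a national range: "Indonesia lags behind WHO recommendations with only 15 to 40 % exclusively breastfeeding".
- The only loss the paragraph mentions is exclusion at screening.

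The analysis text in the same section defines the binary outcome as exclusive breastfeeding for 6 months. It plans an intention-to-treat analysis of all randomized women, with multiple imputation for missing data.

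On follow-up, the section Results of screening, enrollment, and preliminary follow-up says: "So far, the 1-year follow-up is 90.1 % complete". The Discussion says of accurate and complete follow-up: "This is particularly challenging in BRAVO, as it deals with young families in a highly mobile culture".

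**The concern.** A power figure quoted for the number allocated holds only if every allocated woman contributes an outcome. The article reports that follow-up is not complete, and it plans imputation because outcomes will be missing. Imputation keeps each woman in the denominator but does not in general restore the information lost with her outcome.

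This sentence is the only power statement for a comparison between the randomized arms, so a non-significant breastfeeding result would be judged against it. The margin is also thin. The detectable difference is described as just under 10 points and the meaningful difference starts at 10, so a modest loss of information can move the first past the second.

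**Working it through.** **Inputs from the article.** 500 per arm allocated; power 90 %; significance level 0.05; meaningful difference 10 points; interim 1-year completeness 90.1 %; national exclusive breastfeeding 15 % to 40 %.

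**Assumptions.** Two-sided test (sidedness is not stated). Control rate scanned, because none is stated. Known 6-month feeding outcomes taken as 95 % (500 × 0.95 = 475 per arm) or 90 % (500 × 0.90 = 450 per arm), with nothing recovered from the missing women.

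**Formula.** Two-proportion z-test with pooled variance under the null. With control rate p₁, intervention rate p₂ = p₁ + d, and p̄ their mean:

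power = Φ( [ d√n − 1.96·√(2p̄(1−p̄)) ] / √(p₁(1−p₁) + p₂(1−p₂)) )

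**Step 1: reproduce the printed figure.** Take p₁ = 0.30 and d = 0.0975, so p₂ = 0.3975 and p̄ = 0.34875. Then √(2p̄(1−p̄)) = 0.6740 and √(p₁(1−p₁) + p₂(1−p₂)) = 0.6704. With n = 500, d√n = 2.1802, and (2.1802 − 1.3210)/0.6704 = 1.28, which is 90 % power. Solving for d at other control rates gives 9.35 points at 25 %, 9.5 at 27 %, 9.75 at 30 % and 10.0 at about 34.5 %. The printed figure therefore reproduces with 500 analysed per arm. A one-sided test would never need more than about 9.2 points, so the two-sided reading fits better.

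**Step 2: same difference, fewer outcomes.**

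- n = 475: d√n = 2.1250; (2.1250 − 1.3210)/0.6704 = 1.20; power 88.5 %.
- n = 450: d√n = 2.0683; (2.0683 − 1.3210)/0.6704 = 1.11; power 86.8 %.

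This barely depends on the control rate. The two square-root terms are nearly equal, so for any difference that has 90 % power at 500 per arm, power at a fraction f of that number is close to Φ((1.96 + 1.2816)·√f − 1.96). That gives 88.5 % at f = 0.95 and 86.8 % at f = 0.90.

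**Step 3: what happens to the 10-point threshold.** This does depend on the control rate.

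| Control rate | Detectable at 90 % power, n = 500 | n = 475 | n = 450 | Power for 10 points, n = 450 |
|---|---|---|---|---|
| 15 % | 8.0 | 8.3 | 8.5 | 96.4 % |
| 20 % | 8.8 | 9.0 | 9.3 | 93.5 % |
| 25 % | 9.35 | 9.6 | 9.9 | 90.7 % |
| 30 % | 9.75 | 10.0 | 10.3 | 88.3 % |
| 40 % | 10.2 | 10.4 | 10.7 | 85.6 % |

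With 450 per arm, 10 points keeps at least 90 % power up to a control rate of about 26 %. With 500 per arm the limit is about 34.5 %. Between these two rates, missing outcomes alone carry the detectable difference past the meaningful threshold.

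**The case against.** The strongest reply has four parts.

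1. *The sentence is not an arithmetic error.* This stands. The figure reproduces, and the text says openly that the 500 are women allocated. The fault is in what the figure is taken to describe, not in how it was computed.

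2. *90.1 % is the wrong retention figure for this outcome.* This largely stands. It is an interim figure at 1 year, while the outcome is at 6 months. Feeding is asked about monthly. Non-attenders get reminders and home visits, and home visits also collect feeding data from women who discontinue or deviate and still live in the Jakarta area. A woman known to have stopped exclusive breastfeeding before she was lost already has her outcome. Six-month completeness may therefore be better than 90 %, but the article does not report it. Recovery is also partial, because it does not reach families who leave the area. Hence the range of 90 % to 95 % above.

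3. *The 1000 was not solved from this calculation, and the loss is small.* Both are true. The loss is 1.5 to 3.2 power points, or about half a percentage point or less in detectable difference. That limits the weight of the point but does not make the printed power right.

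4. *All randomized women are analysed, with imputation.* This settles the analysis set. It does not in general settle the information available.

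Two stronger readings are tempting. One is that the trial cannot deliver 90 % power for a meaningful difference. The documents do not support this: the control rate is unstated, and at about 26 % or lower 10 points keeps at least 90 % power with 450 per arm. Near the 0 % that the article cites for usual care at 6 months, that power is practically 100 %. The other is that power collapses for the cardiovascular measurements at 4 to 5 years. The article claims no power for that randomized comparison, gives no retention to that age, and attaches its 80 % figure only to the 54 versus 54 feeding comparison, which it says the trial does not yield.

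**Conclusion.** The point holds in a limited form. The 90 % power belongs to a trial with complete outcomes in 500 women per arm, and the article's own follow-up report makes complete outcomes unlikely. For the difference that 500 per arm detects with 90 % power, a fair figure is about 88.5 % with 95 % of 6-month feeding outcomes known, and about 87 % with 90 % known. Whether 10 points itself keeps 90 % power depends on a control rate the article does not give: it does at about 26 % or lower, and at 30 % the detectable difference reaches about 10.0 to 10.3 points.

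These figures rest on a two-sided test, equal loss in both arms, no information recovered from women with missing outcomes, and an assumed 6-month completeness. The shortfall is modest and does not call the trial's size into question. It is worth correcting because the statement is relied on and the correction is cheap.

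**What to change.** In the sample-size paragraph, restate the power, or the detectable difference, for the number of women expected to have a 6-month feeding outcome, and name the assumed control rate of exclusive breastfeeding. As a provisional statement, 450 to 475 women per arm give about 87 % to 88.5 % power for the difference now quoted; at a 30 % control rate they give 90 % power for about 10.3 to 10.0 points. Label the completeness as an assumption, and replace it with the actual 6-month completeness once known rather than carrying over the 1-year figure.

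The cost is wording only. The stated power becomes slightly less favourable, and neither enrolment nor the analysis changes.

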### Endpoints

BRAVO deals with studying every child’s first year; in addition, it will follow children until at least their 5^th^ year of life for carotid artery wall measurements, pulmonary function, anthropometry, and disease history. A general scheme of measurements and timing throughout BRAVO follow-up is presented in Table 3. Outcome assessors and data analysts are being blinded about the participants’ assignment to interventions. Retention of mothers and children at the age of 5 years will be optimized by proactively contacting the mothers by telephone or in writing.

**Table 3 Tab3:** Schedule of enrollment, interventions, and assessments

	Study period															
	Enrollment	Allocation	Post-allocation													Close-out
TIME POINT	Gestation week		Birth	month												
	*24–36*	32–36	*1*	*2*	*3*	*4*	*5*	*6*	*7*	*8*	*9*	*10*	*11*	*12*	*…*	*48–60*
ENROLLMENT:																
Eligibility screen	X															
Informed consent	X															
Allocation		X														
INTERVENTIONS:																
Antenatal intervention		X														
Postnatal home visit			X													
Biweekly postnatal contacts																
Postnatal visits			X	X		X		X			X			X		
Telephone calls			X	X	X	X	X	X	X	X	X	X	X	X		
*SMS*			X	X	X	X	X	X								
ASSESSMENTS:																
Maternal ad family data		X														
Lung function SOT			X					X								
Lung spirometry														X		X
Feces sampling			X	X		X		X			X			X		
Breastmilk sampling			X	X		X		X			X			X		
Diary upper/lower RTD, allergy, infections			X	X	X	X	X	X	X	X	X	X	X	X	X	
Blood pressure measurement			X	X		X		X			X			X		X
Anthropometry			X	X		X		X			X			X		X
Vascular US carotid artery test																X
Pulse-wave velocity/stiffness																X
Echocardiography cardiac function																X
IGF-1, IGFBP-3, leptin levels, fibrinogen*														X		X

*SMS* short message service, *SOT* single occlusion technique, *RTD* respiratory tract disease, *US* ultrasound, *IGF-1* insulin-like growth factor 1, *IGFBP-3* insulin-like growth factor binding globulin 3

Primary outcome I includes the monthly questionnaire/telephone call to discuss feeding patterns (breast/formula feeding habits).

Primary outcome II includes the vascular wall characteristics at 4 years old (thickness of carotid intima-media, distensibility, and elastic modulus) (see Table 4).

**Table 4 Tab4:** Cardiovascular endpoint measurements

	Methods	Arterial segment	Timing
Vascular ultrasound	Carotid artery		48 to 60 months

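### Breastfeeding duration is known only as a lower bound for some women, but the planned linear regression on (transformed) duration has no way to use that bound

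*Protocol article*

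**What the plan says.** All references are to the protocol article.

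- **Method.** The section on data management, randomization, statistical power and data analysis says that duration will be studied "by using linear regression with (transformed) duration as the dependent variable and a group indicator as the independent variable". The transformation is in brackets and is not named.
- **Recording.** Under Endpoints, "Primary outcome I includes the monthly questionnaire/telephone call to discuss feeding patterns". Table 3 marks telephone calls in months 1 to 12 and none at the 48–60 month visit.
- **Window.** The Discussion says that "the follow-up, to be done for the first year of life, is designed to follow regular care".
- **Completeness.** The preliminary results state: "So far, the 1-year follow-up is 90.1" % complete. No split by arm is given.
- **Population.** Women are eligible if they "plan to give breastfeeding for no longer than 2 months, if at all".
- **Missing data.** "Missing data will be analytically addressed using multiple imputation regression techniques". Women still feeding at their last contact are not mentioned.
- **Companion analysis.** "The chance of successful exclusive breastfeeding for 6 months (yes/no) will be compared" between arms by relative risk, with a number needed to treat.

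**The concern.** A woman still breastfeeding at month 12, or lost earlier while still feeding, has a duration known only to be at least as long as observed. Linear regression needs one number per woman. The analyst can enter the cut-off time as the duration, drop the woman, or impute a value. Entering the cut-off understates her duration. Dropping her removes the longest feeders selectively. Imputation works only if the imputed values are held above the observed time, and the plan does not say that they will be.

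The population adds a second difficulty. Some women may never breastfeed, so zero durations are to be expected. A log transform is undefined at zero, and an effect on a transformed scale is not a number of months gained.

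The Discussion says that the trial's success depends on the breastfeeding contrast between arms, and that the contrast depends on the distribution of duration in each arm. A misstated duration contrast would therefore also affect how the vascular results are read.

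**Working it through.** The article states no figure for duration, so there is none to reproduce. Its figures for proportions (500 per arm, a difference of almost 10 %, 90 % power) and for intima-media thickness (54 per group) do not enter this point.

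**Inputs from the article:** cut-off at 12 months (Table 3); 1-year follow-up 90.1 % complete, so 100 − 90.1 = 9.9 % incomplete, taken as 10 %.

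**Assumptions, not in the article:** exponential durations with median M; a share p of each arm lost at a time uniform over 0–12 months; recorded time (the earliest of cessation, loss and month 12) entered as the duration. With only a group indicator, the regression coefficient is the difference in mean recorded time.

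**Formulas**

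- Full mean: m = M / ln 2.
- Mean within 12 months: R = m(1 − 2^(−12/M)).
- Mean recorded time if lost: L = m[1 − (m/12)(1 − 2^(−12/M))].
- Mean recorded time in an arm: R − p(R − L).

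| M (months) | m | R | L | R − L | Still feeding at 12 months |
|---|---|---|---|---|---|
| 2 | 2.885 | 2.840 | 2.202 | 0.638 | 1.6 % |
| 3 | 4.328 | 4.058 | 2.865 | 1.193 | 6.3 % |
| 4 | 5.771 | 5.049 | 3.343 | 1.707 | 12.5 % |
| 6 | 8.656 | 6.492 | 3.973 | 2.519 | 25.0 % |
| 9 | 12.984 | 7.831 | 4.510 | 3.321 | 39.7 % |

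**Equal loss, p = 0.10 in both arms**

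For medians 4 v 6:

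- full mean difference 8.656 − 5.771 = 2.885;
- difference within 12 months 6.492 − 5.049 = 1.443;
- regression 1.443 − 0.10 × (2.519 − 1.707) = 1.36 (simulation with 500 per arm gave 1.35).

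| Medians | Full difference | Within 12 months | Regression | % of full | % of 12-month |
|---|---|---|---|---|---|
| 2 v 3 | 1.44 | 1.22 | 1.16 | 81 | 95 |
| 4 v 6 | 2.89 | 1.44 | 1.36 | 47 | 94 |
| 6 v 9 | 4.33 | 1.34 | 1.26 | 29 | 94 |

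The large gap from the full difference comes mostly from the 12-month cut-off. Early loss accounts for the remaining 5–6 %.

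**No true effect**

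With equal loss the two arms are shortened alike and the difference is zero. With 15 % loss in one arm and 5 % in the other, the false difference is (0.15 − 0.05)(R − L):

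- median 2: 0.10 × 0.638 = 0.06 month (simulation 0.07);
- median 4: 0.10 × 1.707 = 0.17 month (simulation 0.18);
- median 6: 0.10 × 2.519 = 0.25 month (simulation 0.25).

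The sign depends on which arm loses more. Greater loss under usual care produces a false gain; greater loss under empowerment hides a gain.

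**Sensitivity to the model.** A separate simulation added never-starters (10 % v 5 %) to medians of 6 v 9, with 9.9 % loss per arm. The full difference was 4.5 months, the 12-month difference 1.6 and the regression estimate 1.5, again 94 % of the 12-month target.

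**The case against.** The strongest case against has five parts.

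1. *The article never says that cut-off times are entered as durations, and multiple imputation can be bounded.* This stands. A reader might infer from the regression sentence that lower bounds will be treated as true durations; the text does not go that far. What remains is that the named method has no place for a bound and the imputation sentence mentions none.

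2. *The log transform is not named, and the bracket makes any transformation optional.* This also stands. Zeros alone do not bias a difference in raw means at about 500 per arm. They matter only if a transformation such as the log is chosen.

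3. *Against mean duration within 12 months the shortfall is only about 5–6 %.* Correct. The comparison with the full mean difference is fair only because the article sets no 12-month horizon for duration. The proposed fix does not estimate the full difference either.

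4. *Women who plan at most 2 months may stop early, and duration may mean exclusive breastfeeding.* In either case few would be censored at month 12 and the problem is small. Planned duration is not achieved duration, however, the article gives no achieved durations, and the sentence does not limit itself to exclusive feeding.

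5. *Unequal loss has no documentary basis.* Retention measures apply to both arms, and women who discontinue but stay in Jakarta are visited at home to collect feeding data. A reader might infer differential loss because only the empowerment arm receives lactation visits, weekly messages and support calls. That is possible, but the article gives no completeness by arm, so 15 % v 5 % is purely illustrative.

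**Conclusion.** The point holds in a limited form. The article fixes an analysis that cannot use the partial information from women still feeding at month 12 or lost while feeding, and nothing else it states does so.

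If recorded time is entered as the duration, the estimate falls well short of the full mean difference (about 1.35 v 2.9 months at assumed medians of 4 v 6) and 5–6 % short of the 12-month difference with equal loss. Unequal loss would add an error of either sign, about 0.1 to 0.25 month for medians of 2 to 6 at an assumed 15 % v 5 % with no effect. All these sizes rest on the exponential shape, the medians and the loss pattern, none of which the article supplies.

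A reader might conclude that the duration comparison is biased in any event. The documents do not support that: with no effect and equal loss there is no bias, and with short durations the error is slight. The 6-month relative risk, the number needed to treat and the sample size are unaffected. The change is worth making because a better-suited method is available for data already being collected.

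**What to change.** Make time to cessation of breastfeeding the main analysis of duration:

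- count women who never breastfed as events at time 0;
- censor women still feeding at their last contact or at 12 months, whichever is earlier;
- report Kaplan-Meier curves by arm and the difference in restricted mean duration with a 95 % confidence interval, to 6 months for exclusive and to 12 months for any breastfeeding.

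This keeps the zeros, uses the lower bounds and gives a result in months. A log-rank test, or an interval-censored model to reflect monthly recording, can support it. The linear regression may stay as a supporting analysis, with a stated rule for women whose duration is only a lower bound.

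The cost is about one sentence in the analysis section and no new data. There are two limits: the estimate speaks only to the stated horizon, and it assumes that censoring before that horizon is non-informative. Loss should therefore be reported by arm beside it.
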